### Study endpoints

Primary endpoint is the occurrence of a thromboembolic or bleeding event or death within a 9 months study period. Secondary endpoints are the occurrence of other ADR, the number of hospital admissions due to ADR, the number of specialist referrals due to ADR, the number of medication changes, the patients’ adherence to the medication regimen, time to death, health-related quality of life, costs of medication and of additional general practitioner (GP) consultations and hospital treatments as well as a cost-benefit analysis.

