### Randomization

Randomization is performed upon receipt of the CRF and is stratified by GP-practice and gender to account for potential influence of GP and gender and to ensure balanced groups within each stratum. Randomization lists are provided by the Biostatistics Unit of the Federal Institute for Drugs and Medical Devices Bonn. According to the allocated study-arm, either a standardized or an individualized risk assessment leaflet is written and sent out to the GP in duplicate, as one copy will be handed out to the patient.

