### Follow-up and blinding

Follow-up time is 9 months for each patient. Overall, 4 visits are scheduled at intervals of 3 months. The study starts at visit 1 when the patient receives the risk assessment leaflet. During this visit, the general practitioner hands out the leaflet and explains its contents to the patient. It is at the discretion of the GP in which way and to what extent he uses the provided information for further treatment, no specifications are made. Patients are considered to be blinded to group assignment, since group assignment is not actively communicated at any time and both risk assessment leaflets have a very similar layout.

During each visit, the following information is documented in the CRF: reason for GP-consultation, vital signs, ECOG score for the patient’s physical condition [40], adverse events (bleeding events, thromboembolic events and others), number of GP-consultations in the meantime, specialist referrals, hospital admissions, sick leaves, remedies and aids and other procedures (e. g. emergency department visits, rehabilitation etc.). Data about anticoagulation/antiplatelet therapy regimen, medication and diagnoses are updated during each visit. Additionally, patients are asked to fill in questionnaires about their health related quality of life (SF-36 [33], filled in at each visit), their adherence to the medication regimen [34] (filled in at the beginning and end of the study) and their social state (filled in once at the beginning of the study).

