### Statistical analysis

#### Primary endpoint

The proportion of patients with an event (i. e. thromboembolic or bleeding event or death) will be compared between the two study arms using the Cochran-Mantel-Haenszel-Test stratified by gender and medical practice. Following the intention-to-treat principle, all randomized patients will be analyzed according to their randomized allocation. Dropouts will be counted as treatment failure in primary analysis. Risk reduction is estimated by the Mantel-Haenszel estimator of the common relative risk with the corresponding 95 % confidence interval. Additional sensitivity analyses will be performed, which include evaluation of different covariate structures.

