### Secondary endpoints

The SF-36-questionnaire for health related quality of life will be analyzed with a mixed model for repeated measurements using an unstructured covariance matrix . The mixed model contains the categorical covariates treatment, visit, gender and medical practice, a continuous covariate for the baseline SF-36-score and a treatment by visit interaction. Evaluation of drug-associated morbidity involves descriptive analysis of the number of patients with severe adverse drug reactions, the number of hospital admissions and specialist referrals due to ADR and the number of medication changes during the study period. The adherence scale will be evaluated using the non-parametric Wilcoxon-test. Survival time will be analyzed using a log-rank-test stratified by gender and medical practice. Additionally, a Cox-regression, which includes covariates treatment, gender, medical practice, age group and anticoagulant as well as a treatment by gender interaction, will be performed as a sensitivity analysis. The direct costs of the prescribed medication, unexpected GP-visits and hospitalizations will be collected and used for a cost-effectiveness analysis to compare the two study groups. In this context, two types of health outcomes will be examined. Firstly, the incidence of adverse events and secondly, the quality-adjusted-life-years (QALY) measures using the SF-36-questionnaire.

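### The adherence comparison, as written, names neither the baseline score nor gender or practice; the test stays valid but gives up precision (minor)

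*Protocol article*

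**What the plan says.** Adherence is a secondary endpoint; Study endpoints lists "the patients’ adherence to the medication regimen, time to death, health-related quality of life" among others. Under Follow-up and blinding, the adherence questionnaire is "filled in at the beginning and end of the study", so each patient has a starting value. Under Randomization, allocation "is stratified by GP-practice and gender to account for potential influence of GP and gender and to ensure balanced groups within each stratum".

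The analysis is fixed under Secondary endpoints: "The adherence scale will be evaluated using the non-parametric Wilcoxon-test". The sentence does not say whether the end score or the change from the start is compared.

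The neighbouring analyses are more explicit:
- The primary endpoint is compared "using the Cochran-Mantel-Haenszel-Test stratified by gender and medical practice".
- For SF-36: "The mixed model contains the categorical covariates treatment, visit, gender and medical practice, a continuous covariate for the baseline SF-36-score", plus a treatment-by-visit interaction.
- For time to death: "Survival time will be analyzed using a log-rank-test stratified by gender and medical practice". The Cox regression offered as a sensitivity analysis also includes gender and practice.

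**The concern.** Each of the other analyses for which the article names a test or model includes gender and practice. The one for the other repeated questionnaire also includes its baseline score. Adherence is the exception. The sentence directly after it says that the log-rank test is stratified, so the natural reading is that the Wilcoxon test is a plain two-group comparison.

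What is at stake is efficiency. A patient's starting score probably predicts the final one, and a comparison that ignores it leaves explainable variation in the error. A real difference in adherence would then be estimated less precisely than the collected data allow.

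**Working it through.** **The plan's own figure.** The article states a sample size only for the primary endpoint: 10 % versus 5 %, 80 % power, 435 per arm. Two-sided α = 0.05 is assumed, because the article gives none. With pooled variance:

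n = [1.960·√(2·0.075·0.925) + 0.8416·√(0.10·0.90 + 0.05·0.95)]² / 0.05² = (0.7301 + 0.3121)² / 0.0025 ≈ 434.4, rounded up to 435.

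This reproduces, and the present point does not affect it. The 435 per arm is used below as the number with an end-of-study score.

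**Assumed inputs.** The article gives no standard deviation, effect, baseline-to-end correlation (ρ) or practice intraclass correlation (ICC) for adherence. I take ρ = 0.3, 0.5 and 0.7, and ICC = 0, 0.05 and 0.15.

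**Normal approximation.** The standardised effect with 80 % power for an unadjusted comparison of end scores is

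d = (1.960 + 0.8416)·√(2/435) = 0.190.

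Baseline adjustment multiplies the variance by 1 − ρ². A comparison of change scores multiplies it by 2(1 − ρ). Power is Φ(2.8016/√(variance ratio) − 1.960).

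| ρ | Ratio, adjusted | Power, adjusted | Ratio, change | Power, change |
|---|---|---|---|---|
| 0.3 | 0.91 | 83.6 % | 1.40 | 65.8 % |
| 0.5 | 0.75 | 89.9 % | 1.00 | 80.0 % |
| 0.7 | 0.51 | 97.5 % | 0.60 | 95.1 % |

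The gain over 80 % is therefore about 4, 10 and 18 points. As effective sample size, 1/(1 − ρ²) − 1 gives 10 %, 33 % and 96 %.

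**Simulation with a discrete score.** The setting was 54 practices of 16 patients (864 in all), allocation balanced within practice and gender, an assumed 0–8 score with a ceiling, a shift of 0.19 on the underlying scale, and 1,500 runs per setting. Stratified means a van Elteren test over practice by gender. The last column is the same test after regression on baseline rank.

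| ICC | ρ | Plain Wilcoxon | Stratified only | Stratified and baseline-adjusted |
|---|---|---|---|---|
| 0 | 0.3 | 75.4 % | 72.3 % | 72.6 % |
| 0 | 0.5 | 75.7 % | 71.4 % | 79.5 % |
| 0 | 0.7 | 75.9 % | 72.5 % | 90.4 % |
| 0.05 | 0.3 | 76.6 % | 75.2 % | 75.1 % |
| 0.05 | 0.5 | 77.1 % | 75.0 % | 80.8 % |
| 0.05 | 0.7 | 74.9 % | 73.8 % | 90.6 % |
| 0.15 | 0.3 | 76.1 % | 78.5 % | 76.9 % |
| 0.15 | 0.5 | 78.3 % | 78.6 % | 82.1 % |
| 0.15 | 0.7 | 77.2 % | 77.9 % | 91.1 % |

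The Monte Carlo standard error is about √(0.75·0.25/1500) = 1.1 points. Stratification alone loses up to about 4 points without clustering and gains at most about 2 at ICC 0.15. Adding baseline gives no clear gain over the plain test at ρ = 0.3, about 4 points at 0.5, and about 14 to 16 at 0.7.

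**Type I error of the plain test.** The simulated rates were 4.9–6.5 % at ICC 0, 4.7–5.5 % at ICC 0.05 and 3.2–4.4 % at ICC 0.15, with a Monte Carlo standard error of √(0.05·0.95/1500) = 0.6 points. I read this as nominal without clustering (the 6.5 % is one of nine settings) and conservative with it.

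**Stratum size.** With 40–80 practices and two genders there are 80–160 strata. For 960 patients that is an average of 960/160 = 6 to 960/80 = 12 per stratum, which explains why full stratification can cost power.

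**The case against.** The strongest reply is that the gap is read from silence. The article calls the test neither unadjusted nor unstratified. A Wilcoxon test on the change from baseline would use the starting score, and a condensed article may leave such details to a full protocol or analysis plan that is not shown. This stands in part: the wording does not prove a plain test on end scores. But the method is stated rather than left open, the neighbouring sentences name strata where strata are meant, and a change score is less efficient than adjustment at every correlation examined.

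A second reply is that the Wilcoxon test is a sound choice for a non-normal scale, and that a model adds assumptions. This is correct, and it is the reason to keep the test as a sensitivity analysis.

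Three stronger readings are tempting and are not supported:
- A reader might infer that an analysis that does not mirror the randomisation has a standard error that is too large and is therefore flawed. The excess arises only with practice clustering, for which the article gives no figure. Where it arises the test is conservative, and stratifying alone recovers little.
- A reader might take the power gain as established. It depends wholly on an assumed correlation, and in the discrete-score simulation it disappears at 0.3.
- A reader might regard adherence as a main route of the leaflet's effect. The article does not say so. The individual content concerns risk scores, interactions, renal function and genotype, and its use is left to the practitioner.

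**Conclusion.** The point holds as a minor one. As written, the adherence comparison leaves unused, or does not name, a baseline score that is collected and the two factors used in randomisation, and so differs from the SF-36 analysis beside it. The comparison is valid: no bias and no inflation of type I error is shown, and the primary analysis and the 435 per arm are unaffected.

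The loss is precision on one secondary endpoint, and it comes mainly from the baseline score. By normal approximation it is about 4 to 18 power points for correlations of 0.3 to 0.7. With a discrete score and full stratification it runs from nothing clear at 0.3 to roughly 15 points at 0.7. Both ranges rest on assumed correlations, clustering and score shape.

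**What to change.** State that the end-of-study adherence score is the outcome. Analyse it with a proportional-odds model, or a rank-based covariance analysis, containing treatment, baseline score, gender and practice. Choose one of the two before the data are compared by arm. Where a model is used, enter practice as a random intercept rather than as 80–160 fixed practice-by-gender strata. Report the adjusted treatment effect with its 95 % confidence interval, and keep the Wilcoxon test as a sensitivity analysis.

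The change takes a sentence or two and needs no new data, visits or patients. The small downside is a model assumption (proportional odds), which the retained Wilcoxon test covers.

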### Sample size

Sample size calculation was based on the primary endpoint and its primary analysis. Preceding studies reported incidence rates ranging from 8 to 10.6 % for thromboembolic and bleeding events in a population of elderly polymedicated patients on oral anticoagulants [32, 35]. Thus, for sample size calculation, we assumed an incidence rate of 10 % in the control group, which we assumed to be reduced by half as a result of the individualized risk assessment (i.e. to 5 %). To detect this anticipated difference with a power of 80 % using the Cochran-Mantel-Haenszel test (assuming equal effects in all strata), a sample size of 435 patients per arm is required. Assuming a dropout rate of 10 % about 960 patients need to be included in the study.

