### Recruitment

The study is conducted in the area of Bonn, Cologne and the Rhine-Sieg-district, Germany. 40–80 GP-practices situated in this area participate in the study. After being instructed by the Institute of General Practice and Family Medicine Bonn, the general practitioners create a list of eligible patients. They name the number of patients to the institute and in return obtain in a first step a random selection of 10 patients to be asked by the GP to participate in the study. This random selection is performed using prefabricated lists provided by the Department of Biostatistics of the Federal Institute for Drugs and Medical Devices Bonn to avoid selection bias. Overall each GP-practice is planned to enroll 12–24 patients. The workflow of the IDrug study is illustrated in Fig. 1.

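### The sensitivity Cox model for survival includes a treatment-by-gender interaction and names no overall contrast, so as written it does not check the log-rank result; its 40–80 practice terms also cannot all be estimated

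*Protocol article*

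**What the plan says.** The subsection on secondary endpoints in the Protocol article's statistical analysis plans two analyses of survival time. The main one is a log-rank test in which gender and practice are strata. The second is labelled a sensitivity analysis: "Additionally, a Cox-regression, which includes covariates treatment, gender, medical practice, age group and anticoagulant as well as a treatment by gender interaction".

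Practice is therefore a stratum in the log-rank test but a covariate in the Cox model. The SF-36 mixed model in the same subsection lists practice among its categorical covariates, so one fixed effect per practice is the natural reading. No coding and no overall treatment contrast is given for the Cox model.

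The number of practices comes from the Recruitment section: "40–80 GP-practices situated in this area participate in the study". No expected number of deaths appears anywhere. The nearest figures are the planning rates under Sample size: "we assumed an incidence rate of 10 % in the control group", halved to 5 % in the test group. Their source is described so: "Preceding studies reported incidence rates ranging from 8 to 10.6 % for thromboembolic and bleeding events". Death is not mentioned in that source rate, although it is part of the composite primary endpoint.

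**The concern.** A sensitivity analysis should ask the same question as the analysis it supports, under different assumptions. The stratified log-rank test asks whether survival differs between the arms overall. Once a treatment-by-gender term is in the Cox model, the line labelled treatment no longer answers that question unless a contrast is specified. A reader could take a less precise, one-gender hazard ratio as confirming or contradicting the main result.

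The second matter is the size of the model. Death is only one component of a composite that is itself expected in fewer than 100 patients, yet practice alone contributes 39–79 coefficients. Some of these cannot be estimated, because a practice with no death gives no finite value.

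**Working it through.** **Reproducing the plan's own figure.** With 10 % against 5 %, two-sided α = 0.05 (assumed, since the article does not state it), 80 % power and no continuity correction:

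n = [1.960·√(2·0.075·0.925) + 0.842·√(0.10·0.90 + 0.05·0.95)]² / 0.05² = (0.730 + 0.312)² / 0.0025 ≈ 434.4, which rounds up to 435 per arm. This matches "a sample size of 435 patients per arm is required". The planned total is 960.

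**Events implied by the design.** 480 × 0.10 + 480 × 0.05 = 72 composite events in 960 patients. In 870 patients it is 435 × 0.15 = 65. Deaths are a subset of these.

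**Coefficients in the Cox model as written.** Treatment 1, gender 1, interaction 1, practice 39–79, age group at least 1, anticoagulant at least 1.
- 40 practices: 1 + 1 + 1 + 39 + 1 + 1 = 44.
- 80 practices: 1 + 1 + 1 + 79 + 1 + 1 = 84.
- With four age groups (3 terms) and all nine named index drugs (8 terms): 53 and 93.

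**Comparison with events.**
- At 80 practices, 84 exceeds all 72 composite events. Deaths would exceed 84 only if mortality were above 84/960 = 8.75 %.
- At 40 practices, deaths exceed 44 only if mortality is above 44/960 = 4.6 %. Deaths would then be more than 44/72 = 61 % of all planned composite events.

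**Practices with no death.** Assuming equal practice size and equal risk r, the expected number is K·(1 − r)^(960/K). Mortality is an assumption, shown over a range:

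| Mortality | Deaths | Deaths per coefficient, 40 / 80 practices | Practices with no death, of 40 / of 80 |
|---|---|---|---|
| 2 % | 19 | 0.44 / 0.23 | 24.6 / 62.8 |
| 3 % | 29 | 0.65 / 0.34 | 19.3 / 55.5 |
| 4 % | 38 | 0.87 / 0.46 | 15.0 / 49.0 |
| 5 % | 48 | 1.09 / 0.57 | 11.7 / 43.2 |
| 6 % | 58 | 1.31 / 0.69 | 9.1 / 38.1 |

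**What the interaction does to the target.** Under reference coding, the treatment coefficient is the log hazard ratio in the reference gender. In simulated trials (60 runs, 40 practices as strata, 5 % control mortality, about 40 deaths) with true hazard ratios of 0.35 and 0.90 in the two genders, the median treatment estimate was 0.37 with the interaction and 0.66 without. Sum-to-zero coding would target √(0.35 × 0.90) = 0.56, the unweighted mean on the log scale.

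**What the interaction does to precision.** With deaths about equal between arms, SE(log HR) ≈ 2/√D.
- All 38.4 deaths: 2/√38.4 = 0.32.
- One gender with half of them: 2/√19.2 = 0.46, a ratio of √2 = 1.41.
- One gender with 40 % of them (15.4 deaths): 2/√15.4 = 0.51, a ratio of 1.58.

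Simulations with about 38–39 deaths and a true hazard ratio of 0.7 agree. The treatment SE was 0.47–0.50 with the interaction and 0.33–0.35 without. Another set, with three age groups and two drug classes, gave 0.52–0.53 against 0.33–0.35.

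**What the practice terms do to the treatment estimate.** Almost nothing. In that last set, the median SE at 40 / 80 practices was:

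| Practice handled as | No interaction | With interaction |
|---|---|---|
| Not in the model | 0.33 / 0.34 | 0.52 / 0.52 |
| Covariates | 0.33 / 0.35 | 0.52 / 0.53 |
| Strata | 0.33 / 0.35 | 0.52 / 0.53 |

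The median treatment estimate was −0.36 to −0.42 in all six models (true value −0.36), and no run diverged.

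**The case against.** Four objections carry weight.

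1. **Coding and contrasts.** The article does not say that a reference-coded coefficient will be read as the overall effect. A contrast could recover an average effect from the same model, and a fuller analysis plan may specify one. This stands as a limit on the claim: the model contains the information, but the text names no quantity to extract. Sum-to-zero coding alone does not settle it, because it weights the genders equally and need not match the model without the interaction (0.56 against 0.66 in the example).

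2. **The practice terms.** A reader might infer from the parameter count that the fit fails, that the treatment estimate becomes unstable, or that its standard errors are too small because of the practice terms. None of this is supported. A practice without deaths has a diverging coefficient, but the partial likelihood has a finite limit and the practice simply drops out, as it does in the stratified log-rank test. The treatment SE is nearly the same with practice as covariates, as strata or left out. Model SEs below the empirical spread were also seen in most practice-stratified fits, so that is not specific to practice covariates.

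3. **Number of deaths.** It is assumed. At 40 practices the comparison turns at 4.6 % mortality, which lies inside the range shown. At 80 practices it does not depend on that range.

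4. **Reach.** Neither the stratified log-rank test nor the Cochran-Mantel-Haenszel analysis of the primary endpoint uses this model. This stands, and it sets the priority.

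**Conclusion.** The point holds in a limited form. The main defect is the interaction. With it, and with no overall contrast named, the treatment coefficient under usual coding describes one gender. Its standard error is about 1.4–1.5 times that of a model without the interaction at an assumed 38–39 deaths, and somewhat more if the reference gender has fewer than half the deaths. As written, the model does not check the overall effect tested by the log-rank test.

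The secondary defect is that practice as a covariate gives at least 44–84 coefficients, some without a finite estimate. This is untidy and avoidable, but it does not damage the treatment estimate.

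The conclusion assumes fixed practice effects, reference coding and a number of deaths that the article does not give. Priority is low: no primary or main secondary result is affected.

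**What to change.** Make the main sensitivity model a Cox regression stratified by medical practice, with treatment, gender, age group and anticoagulant as covariates and no interaction. This treats practice as the log-rank test and the randomisation do, and it yields one overall hazard ratio. At its smallest the model has four coefficients, so 38.4 / 4 = 9.6 deaths per coefficient at 4 % mortality, instead of 0.87 or 0.46. Report treatment by gender as a separate exploratory model.

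The gain in precision comes from removing the interaction. Stratifying by practice only removes terms that cannot be estimated.

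The cost is a change of wording, with no effect on data collection or sample size. The downside is that practice effects are not estimated and that the gender-specific effects move to an exploratory model.

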## Discussion

Objective of the IDrug study is to further investigate individual patient ADR risk factors in a randomized controlled fashion in a real-world clinical setting with elderly patients at high risk for ADR. In contrast to preceding clinical studies, clinical and pharmacogenetic risk factors are not considered in isolation, but together resulting in a comprehensive medication review in form of a risk assessment leaflet. The pragmatic study design does not only allow to obtain valuable data with high external validity, but also paves the way for clinical applicability. For the purpose of realistic conditions, GP-practices were chosen as study sites. Due to the inclusion criteria a broad representative patient population can be acquired. The high risk characteristic of the study cohort might enhance detection rates of adverse drug reactions.

One limitation of the study is that the degree of accuracy of blinding might decrease over the study period, as each GP will receive both versions of risk assessment leaflets and, therefore, might be able to identify study groups during the course of the trial. In contrast, patients only get to see their own risk assessment leaflets. Therefore, it is less likely that blinding is broken for patients. Furthermore, although the provided risk assessment covers the most important risk factors for ADR, some parameters are not included, e. g. drug-disease interactions and missing drug indications. The reason is to keep the leaflets as short as possible to ensure the GP’s and patient’s motivation to read it.

To our knowledge, IDrug is the first randomized controlled trial evaluating the impact of a comprehensive individualized risk assessment including genotyping on adverse drug reactions in a large elderly high risk population. Based on the study results, we will evaluate whether this individualized approach has the potential to increase patient safety in daily routine by reducing ADR in a cost-effective way. This may advance development of rational, evidence-based policies for the application of pharmacogenetic testing in individualized drug therapy in clinical practice.

